## Abstract

**Background:**

Obesity is increasing in the child-bearing population as are the rates of gestational diabetes. Gestational diabetes is associated with higher rates of Cesarean Section for the mother and increased risks of macrosomia, higher body fat mass, respiratory distress and hypoglycemia for the infant. Prevention of gestational diabetes through life style intervention has proven to be difficult. A Finnish study showed that ingestion of specific probiotics altered the composition of the gut microbiome and thereby metabolism from early gestation and decreased rates of gestational diabetes in normal weight women. In SPRING (the Study of Probiotics IN the prevention of Gestational diabetes), the effectiveness of probiotics ingestion for the prevention of gestational diabetes will be assessed in overweight and obese women.

**Methods/design:**

SPRING is a multi-center, prospective, double-blind randomized controlled trial run at two tertiary maternity hospitals in Brisbane, Australia. Five hundred and forty (540) women with a BMI > 25.0 kg/m^2^ will be recruited over 2 years and receive either probiotics or placebo capsules from 16 weeks gestation until delivery. The probiotics capsules contain > 1x10^9^ cfu each of *Lactobacillus rhamnosus* GG and *Bifidobacterium lactis* BB-12 per capsule. The primary outcome is diagnosis of gestational diabetes at 28 weeks gestation. Secondary outcomes include rates of other pregnancy complications, gestational weight gain, mode of delivery, change in gut microbiome, preterm birth, macrosomia, and infant body composition. The trial has 80% power at a 5% 2-sided significance level to detect a >50% change in the rates of gestational diabetes in this high-risk group of pregnant women.

**Discussion:**

SPRING will show if probiotics can be used as an easily implementable method of preventing gestational diabetes in the high-risk group of overweight and obese pregnant women.

## Background

The incidence of gestational diabetes mellitus (GDM), —diabetes mellitus first diagnosed during pregnancy—, is on the rise in concordance with the rise in overweight and obesity in the obstetric population [1]. GDM is associated with short term and long term morbidity for mother and baby. In the short term, women with GDM have an increased risk of developing preeclampsia and delivery by Cesarean section [2,3]. For the infant, maternal GDM increases the risk of excessive adiposity, macrosomia (a birth weight of >4000 g), shoulder dystocia, admittance to the neonatal intensive care unit and neonatal hypoglycemia [4,5]. In the long term, maternal GDM is associated with increased risk of obesity as well as metabolic (type 2 diabetes) and cardiovascular disease in both mother and baby [6-8]. While current therapy, which is focused on normalizing blood glucose levels, is variably successful in reducing the short term complications of GDM, this may not be true for the longer term complications [9]. Therefore, prevention of GDM would be preferable.

The incidence of GDM is higher in women who are overweight or obese prior to falling pregnant [10]. Strategies for the prevention of GDM have until now been restricted to diet and exercise interventions, which have had mixed results [11,12]. Many of these trials have had small sample sizes and their methodological heterogeneity complicates comparability. Additionally, there are substantial barriers to pregnant women engaging in intensive lifestyle intervention programs [13,14].

The role of the gut microbiome as a modulator of metabolic and inflammatory process is currently being investigated. The gut microbiome is the composite of bacterial species present in the gut. Many factors influence the exact gut microbiome species composition in adult life including antibiotic therapy in early life [15], growth and inhibitory factors determined by diet, host and microbial factors as well as luminal pH, osmolarity and organism replication rates [16]. Gut microbiome species have discrete capabilities in generating energy for take-up by the host. The gut microbiome composition is altered in obese humans and animals, although weight loss causes changes in species composition to that resembling the gut microbiome of normal-weight individuals [17,18].

Ingestion of probiotics — “*microorganisms … able to confer defined health benefits on the host*” [19]— is an alternative pathway to alter gut microbiome species composition. The exact effects on metabolic and inflammatory processes in the host exerted by probiotics treatment are dependent on the genus and strain supplied in the probiotics. In the food chain, probiotic cultures are commonly present in variable amounts in dairy products such as yoghurts, fermented foods and some cheeses. It is not known to what extent these food sources alter the gut microbiome and thereby have biological effects outside research settings. Probiotic supplements are available from many outlets but effectiveness is dependent on especially temperature and anaerobic storage conditions, initial dose strain and quality. Probiotic supplementation in pregnancy is considered safe based on the limited safety data available [20].

A recent randomized controlled trial of probiotic intervention in normal weight women in pregnancy reported a decline in the rate of GDM from 34% to 13% with a combined dietary/probiotic supplementation approach [21]. To our knowledge, this trial has not been repeated and in particular, there has been no examination of whether probiotics might offer a useful therapeutic approach for overweight and obese women [22]. If probiotic supplementation were to offer substantial clinical benefit, it would provide a pragmatic approach to the prevention of GDM. This trial aims to provide an answer to these questions.

## Methods/design

### Study design

This is a prospective double blind randomized controlled trial, designed according to the CONSORT guidelines [23]. Our study will investigate the treatment of overweight and obese women with an oral probiotic combination using *Lactobacillus rhamnosus* GG and *Bifidobacterium animalis* subsp. *lactis* BB-12 (Chr. Hansen A/S, Horsholm, Denmark) at a dose of >1 x 10^9^ colony-forming units each per day or placebo (microcrystalline cellulose and dextrose anhydrate capsules – Chr. Hansen). Capsules will be taken once daily from enrolment prior to 16 weeks gestation until birth (Figure 1). 

**Figure 1 F1:**
[figure not shown]
Recruitment at 14–16 wks gestation.

### Outcomes

The primary outcome of the study is the frequency of diagnosis of GDM at 28 weeks gestation by a 75 g oral glucose tolerance test (OGTT) using the criteria of the International Association of the Diabetes and Pregnancy Study Group (IADPSG) [24].

A number of secondary outcomes will be assessed, which are listed in Table 1[25]. 

**Table 1 T1:** Maternal, neonatal and process/intervention secondary outcomes assessed in SPRING

**Maternal**	**Neonatal**	**Process/intervention**
Gestational weight gain	Body composition, anthropometry	Visit attendance
Preeclampsia*	Preterm delivery	Adherence to probiotic/placebo regimen
Induction of labor	Shoulder dystocia	
Cesarean delivery	Hypoglycemia	
Elective	Treatment with supplementary fluids/feeds	
Emergency		
Change in prevalence of *L. rhamnosus* and *B. lactis* in gut microbiome	Nerve palsy	
Change in lipids and inflammatory profile	Admission to neonatal intensive care unit	
Change in dietary indices and physical activity levels between baseline and 28 weeks gestation	Jaundice requiring phototherapy	
	Bone fracture	
	Death: stillbirth or neonatal death	

* Preeclampsia as diagnosed as per the criteria of the international society for the study of hypertension in pregnancy (ISSHP) [25].

### Sample size justification/power calculation

At least one third of pregnant women cared for in Brisbane are overweight and obese, in line with the overweight and obesity rates for the general obstetric population in Australia [26]. In one year, across the Mater Mothers Hospital and the Royal Brisbane and Women’s Hospital, over 3300 overweight and obese pregnant women receive pregnancy care. We anticipate to recruit around 40 women per month across both centers with the recruitment strategy tested in a previous study [27]. Based on the Brisbane cohort within the Hyperglycemia and Adverse Pregnancy Outcome (HAPO) data [28], the rate of GDM amongst women who are overweight and obese is 19.3%. We expect that our screening strategy including a random venous plasma glucose and subsequent OGTT to confirm or exclude the diagnosis of overt diabetes, or early GDM will result in the exclusion of around 5% of women who were included in the HAPO study. This will reduce our expected prevalence of GDM to around 18% (5% of 19.3% is ~ 1%). The previous trial reported a 67% risk reduction [21]. However, even a risk reduction of 50% would be clinically meaningful, and we have based our power calculation on a 50% reduction. To detect a change in the incidence of GDM from 18% to 9%, with a power of 0.8, α of 0.05, and a two-tailed test, the estimated sample size is 226 per group. Allowing for 20% attrition of participants, we will recruit 270 women into each group. We anticipate that it will take 15 months to recruit this sample size.

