### Exclusion criteria

The exclusion criteria for this study are: pregnancy at >16 weeks gestation at recruitment; multiple pregnancy; known pre-existing diabetes, impaired fasting glucose (IFG) or impaired glucose tolerance (IGT); GDM prior to recruitment as diagnosed by early pregnancy glucose testing described below; taking medications likely to influence glucose metabolism (in particular metformin, glucocorticoids and immunosuppressants); medical conditions associated with altered glucose metabolism (in particular Cushing’s syndrome/disease and hepatic cirrhosis); known major fetal abnormality noted on 12 week ultrasound examination; and known ingestion of probiotics via capsules or sachets.

The early pregnancy glucose testing follows a strategy supported by the guidelines of the IADPSG [29]. All women will have their random venous plasma glucose measured. Women with a random venous plasma glucose level of >11.0 mmol/L will be considered as having likely overt diabetes and will undergo appropriate further evaluation with fasting glucose, proceeding to an 75 g OGTT if required. Women with overt diabetes or early GDM will be excluded from this study.

In order to ensure participant safety, we do not want to enrol women with serious early pregnancy disturbances in glucose metabolism. Therefore, to err on the side of caution, we will refer any woman with a random venous plasma glucose between 8.0 and 11.0 mmol/L for a 75 g OGTT. Women who are diagnosed with early GDM on this OGTT will be referred for treatment, and excluded from this study. Conversely, those women with an initial elevated random venous plasma glucose but normal OGTT results will remain eligible for randomization.

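### The 18% control-arm GDM rate does not follow from excluding about 5% of women; depending on what the 5% means, the rate is about 15% to 18.5% and power about 72% to 81% at 226 per group

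*Protocol article*

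**What the plan says.** All the figures are in the protocol article, under Sample size justification/power calculation. For the Brisbane HAPO cohort it states that "the rate of GDM amongst women who are overweight and obese is 19.3" per cent. It expects that early glucose screening "will result in the exclusion of around 5% of women who were included in the HAPO study". It concludes: "This will reduce our expected prevalence of GDM to around 18% (5% of 19.3% is ~ 1%).

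The calculation then runs: "To detect a change in the incidence of GDM from 18% to 9" per cent, "with a power of 0.8, α of 0.05, and a two-tailed test, the estimated sample size is 226 per group". The effect size is relative: "we have based our power calculation on a 50% reduction". The Methods/design part of the abstract repeats 80% power without qualification.

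The Exclusion criteria section says whom the screening removes: "Women with overt diabetes or early GDM will be excluded from this study". A raised screening value alone does not exclude, because "those women with an initial elevated random venous plasma glucose but normal OGTT results will remain eligible for randomization".

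**The concern.** The two halves of the derivation use different bases. The sentence on screening counts 5% of women. The parenthesis takes 5% of the GDM rate and subtracts about one percentage point, with no change to the denominator. If the excluded women had GDM only at the average rate, removing them would leave the prevalence where it was. If they are mostly women who would have counted as GDM cases, which is what a screen that excludes only on diagnosis tends to produce, the prevalence falls by more than one point.

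The effect is set as a 50% relative reduction, so a lower control rate also shrinks the absolute difference to be detected. Both the 226 per group and the stated 80% power rest on the 18%. Anticipated limitations discusses a smaller treatment effect but not a lower control rate.

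**Working it through.** **Inputs from the article.** Source rate 19.3%; about 5% of women excluded; control rate 18%; 50% relative reduction; two-sided α 0.05; power 0.80; 226 evaluable per group; 270 recruited per group with 20% attrition allowed, which leaves 270 × 0.8 = 216.

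**Input not in the article.** f, the share of the excluded women who would have been among the 19.3%. It is varied below.

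**Step 1: reproduce the plan's figure.** Normal approximation for two proportions with pooled variance under the null and no continuity correction, where p̄ = (p₁ + p₂)/2:

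n = [1.960·√(2p̄(1 − p̄)) + 0.842·√(p₁(1 − p₁) + p₂(1 − p₂))]² / (p₁ − p₂)²

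For 18% against 9% this gives 225.1, rounded up to 226, which is the stated number. Power is 80.2% at 226. The formula is sound, so the question is only the 18% that goes into it.

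**Step 2: take the 5% as a share of women, as the sentence says.** Of 100 women, 5 leave and 95 remain. Of the 19.3 cases, 5f leave. The remaining rate is (19.3 − 5f)/95.

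- Excluded women have the average rate (f = 0.193): (19.3 − 0.965)/95 = 19.3%, unchanged.
- All excluded women are cases (f = 1): 14.3/95 = 15.05%.
- To reach 18%: f = (19.3 − 0.18 × 95)/5 = 2.2/5 = 0.44. The article states no such share.

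**Step 3: take the 5% as a share of GDM cases, as the parenthesis suggests.** Cases remaining: 19.3 × 0.95 = 18.3 per 100 women originally considered. About 0.965 of 100 women leave, so with the denominator adjusted the rate is 18.335/99.035 = 18.5%. Screening then excludes about 1% of women, a fifth of what the preceding sentence says.

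**Step 4: power for a 50% reduction, same formula.**

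| Assumption | Control rate | Rate if halved | Power at 226 | Power at 216 | n per group for 80% |
|---|---|---|---|---|---|
| Plan as stated | 18.0% | 9.0% | 80.2% | 78.3% | 226 |
| 5% of women, f = 1 | 15.1% | 7.5% | 71.6% | 69.7% | 277 |
| 5% of women, f = 0.8 | 16.1% | 8.1% | 74.9% | 73.0% | 256 |
| 5% of women, f = 0.5 | 17.7% | 8.8% | 79.3% | 77.5% | 230 |
| 5% of cases, denominator unadjusted | 18.3% | 9.2% | 81.0% | 79.2% | 221 |
| 5% of cases, denominator adjusted | 18.5% | 9.3% | 81.4% | 79.7% | 218 |

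The column for 216 shows what is left if the full 20% attrition occurs. The loss of about 2 points between the two power columns arises even at 18% against 9%. It belongs to the attrition allowance and is a separate matter from the prevalence.

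**The case against.** The strongest reply is that the printed working shows which base was used: 5% was taken of the 19.3%. Read as 5% of GDM cases, this gives 18.3–18.5%, so writing about 18% is slightly conservative and the stated power holds at 226 per group. On that reading the control rate is essentially right. This stands, and it is why the article cannot be said to yield 15% by its own figures. What it does not do is rescue the paragraph, because the sentence on 5% of women then has to be wrong.

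A second reply concerns f. A reader might infer that, since only diagnosed women are excluded, all of them come out of the 19.3%, so that the true rate is 15% and the trial has only 70–72% power. The article does not support that as a fact. It excludes women with overt diabetes as well as early GDM and does not say whether overt diabetes is counted in the 19.3%. Nor does it say that every woman positive before 16 weeks would be positive at 28 weeks. f = 1 is the adverse end of a range, and the 70% figure also includes the separate attrition loss.

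A third reply is that the practical consequence is modest. At 15.05%, 226 per group still gives about 80% power for a reduction of 54.5%, and about 95% for the 67% that the article reports from the previous trial. That is fair as to scale. But the article deliberately bases its calculation on 50%, and its power claim has to hold for that effect.

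**Conclusion.** The point holds as an inconsistency in how the control rate was derived, with a conditional effect on power. As written, 18% does not follow from excluding about 5% of women. It would need 44% of the excluded women to be among the 19.3%, a figure the article does not give.

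If the 5% is of women and at least half of those excluded are cases, the control rate is 15.1–17.7%, and power for a halving at 226 per group is 71.6–79.3%. The shortfall against the stated 80% therefore ranges from under 1 point to about 8 points. If the 5% is of cases, power at 226 is about 81% and only the sentence on women needs correcting. The article does not settle which was meant, so the supportable statement is a range and not a single lower power. The sample-size formula itself is not in question: 226 reproduces exactly.

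**What to change.** In Sample size justification/power calculation, say whether the 5% is a share of all women or of GDM cases. If it is of women, also state the assumed share of excluded women who would have been among the 19.3%. Re-derive the control rate with the denominator adjusted. Replace the unqualified 80% there and in the abstract with power for a 50% reduction across control rates of 15% to 18.5%: about 72–81% at 226 evaluable per group, or 70–80% at 216.

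This is a restatement of two places in the text. It requires no change in enrolment, design or analysis. The cost is that the stated power may become less favourable.

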### Analysis

#### Analysis methods

Data will be analysed using the intention-to- treat principle and no intermediate analyses are scheduled. The primary outcome of the study is diagnosis of GDM at 28 weeks gestation. This will be assessed by a 75 g OGTT. The frequency of GDM will be compared between the groups with binary logistic regression accounting for the initial stratification by site and BMI catrgory. The secondary outcomes will be analyzed with general linear models for continuous outcomes and logistic regression for binary outcomes. All data will be summarized by mean and standard deviation for continuous variables and frequencies for categories.

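### Recruiting 270 per group with the stated 20% attrition leaves 216 women, not the 226 required, so planned power is about 78% rather than 80% (minor; wrong as written)

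*Protocol article*

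**What the plan says.** The section on sample size justification and power sets the target as follows: "To detect a change in the incidence of GDM from 18% to 9" per cent, "with a power of 0.8, α of 0.05, and a two-tailed test", and concludes that "the estimated sample size is 226 per group". It then adds the allowance for losses: "Allowing for 20% attrition of participants, we will recruit 270 women into each group".

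The abstract carries the total and the power forward: "Five hundred and forty (540) women with a BMI > 25.0 kg/m^2^ will be recruited over 2 years", and "The trial has 80% power at a 5% 2-sided significance level to detect a >50% change in the rates of gestational diabetes".

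Under Analysis methods, the primary comparison is described thus: "The frequency of GDM will be compared between the groups with binary logistic regression accounting for the initial stratification by site" and BMI category. The sample size section takes no credit for that adjustment. Nowhere does the article define attrition in a way that would make 270 recruited women leave 226 evaluable ones.

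**The concern.** Three figures stand next to each other in the sample size section: 226 needed, 20% lost, 270 recruited. Any two of them fix the third, and the printed three do not agree. The primary outcome comes from the glucose tolerance test at 28 weeks, so a woman lost before then contributes no measured primary outcome. Analysis by intention to treat does not supply one.

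What is at stake is the accuracy of the power statement. If losses reach the level the protocol itself plans for, the trial falls short of its own evaluable number, and the 80% in the abstract does not follow from the calculation behind it. There is little slack: the section on anticipated limitations already concedes that a 30% reduction, though clinically important, would not reach significance.

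**Working it through.** **Inputs**, all from the sample size section: p1 = 0.18, p2 = 0.09, two-sided α = 0.05 (z = 1.960), power 0.80 (z = 0.842), 226 evaluable per group, 20% attrition, 270 recruited per group. The abstract's total of 540 confirms equal groups.

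**Step 1: reproduce 226.** Pooled-variance formula without continuity correction, with mean proportion p̄ = (0.18 + 0.09)/2 = 0.135:

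n = [1.960 × √(2p̄(1 − p̄)) + 0.842 × √(p1(1 − p1) + p2(1 − p2))]² / (p1 − p2)²

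- 2p̄(1 − p̄) = 2 × 0.135 × 0.865 = 0.23355; square root 0.4833
- p1(1 − p1) + p2(1 − p2) = 0.1476 + 0.0819 = 0.2295; square root 0.4791
- n = (0.9472 + 0.4032)² / 0.0081 ≈ 225.1, rounded up to 226

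The plan's figure is reproduced exactly.

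**Step 2: apply the attrition.**

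- Remaining from 270: 270 × 0.80 = 216, which is 10 per group (4.4%) below 226.
- Needed to retain 226: 226 / 0.80 = 282.5, so 283 per group or 566 in total. The stated 270 is 13 per group (4.6%) below that.
- Largest loss that 270 can absorb: 1 − 226/270 = 16.3%.
- Likely origin of 270: 226 × 1.2 = 271.2, rounded down. This is an inference.

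**Step 3: power at the number remaining.** Same formula, solved for power:

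power = Φ{[0.09 × √n − 1.960 × 0.4833] / 0.4791}

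| Evaluable per group | Situation | Power, 18% vs 9% |
|---|---|---|
| 270 | no attrition | 86.6% |
| 226 | 16.3% attrition | 80.2% |
| 216 | 20% attrition | 78.3% |

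**Step 4: does the choice of method matter?** At 216 per group, power is 78.8% with unpooled variance, 79.2% with the arcsine method, 79.1% for the exact power of the Pearson chi-square test and 74.0% with continuity correction. All are below 80%. The plan did not use the continuity-corrected form, which would have required 247 per group, so 74.0% is not the relevant figure.

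**Step 5: what effect has 80% power at 216?** Solving for p2 with the pooled formula gives 8.84%, a reduction of 1 − 8.84/18 = 50.9%.

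**The case against.** The strongest reply is that this hardly matters. The shortfall against the nominal 80% is 1.7 points, and the 20% is itself a planning guess. Any loss up to 16.3% preserves 80% power, and with no loss power is 86.6%. Even at 216 per group, 80% power is available for a reduction of 50.9%, so the abstract's phrase about more than 50% is very nearly met. Adjustment for site and BMI category could also change power slightly. All of this stands, and it is why the point is minor. It does not make the printed figures agree.

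One could also read the 20% as a percentage of the evaluable number rather than of those recruited. The 44 extra women per group are 44/226 = 19.5% of 226, so 270 nearly fits. But the sentence speaks of attrition of participants, which ordinarily means the share of enrolled women who are lost, and the article gives no other definition.

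Two stronger readings are tempting, and the document supports neither.

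- A reader might take the word *change* in the abstract as a claim of equal power for a 50% increase, which the calculation does not cover. But the sample size section uses the same word for the move from 18% to 9% and says that the calculation is based on a 50% reduction; the limitations section repeats this. The word is shorthand for the reduction, and a two-sided test does not promise equal power for harm.
- A reader might combine the shortfall with a control-group rate below 18% and conclude that power is much lower. The article plans on 18%, derived from 19.3%. Any lower rate would need an assumption about the women excluded by early glucose testing, which is a separate question and no part of this arithmetic.

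**Conclusion.** Wrong as written, and minor. The stated requirement, attrition and recruitment figures cannot all hold: 270 per group with 20% attrition leaves 216, not 226. On the plan's own formula this means 78.3% power instead of 80%.

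The conclusion assumes that attrition means the fraction of recruited women without a primary outcome, that the full 20% is lost, and that the true rates are exactly 18% and 9%. It would therefore be too strong to say flatly that the trial fails to deliver 80% power: that holds only if losses exceed 16.3% and the effect is no larger than planned. The estimand, the test and the validity of the comparison are untouched.

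**What to change.** Keep 540 women and restate one figure in the sample size section, in one of two ways:

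- state that 270 per group allows for about 16% attrition (270 × 0.84 = 226.8, which keeps 226 evaluable and 80% power); or
- keep the 20% and state that the remaining 216 per group give about 78% power for 18% versus 9%.

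Then align the abstract. The 80% can stay under the first option with the lower attrition allowance, and becomes about 78% under the second. For consistency with the sample size section, the abstract could also describe the target as a 50% reduction, from 18% to 9%; this is optional.

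The cost is wording only, with a slightly less favourable attrition allowance or power figure. Anyone who prefers to keep both 20% attrition and 80% power would need 283 per group, 566 in total, which is 26 more women. Given the size of the shortfall, that is not required.
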